## Abstract

**Background::**

The threat of a possible Marburg virus disease outbreak in Central and Western Africa is growing. While no Marburg virus vaccines are currently available for use, several candidates are in the pipeline. Building on knowledge and experiences in the designs of vaccine efficacy trials against other pathogens, including SARS-CoV-2, we develop designs of randomized Phase 3 vaccine efficacy trials for Marburg virus vaccines.

**Methods::**

A core protocol approach will be used, allowing multiple vaccine candidates to be tested against controls. The primary objective of the trial will be to evaluate the effect of each vaccine on the rate of virologically confirmed Marburg virus disease, although Marburg infection assessed via seroconversion could be the primary objective in some cases. The overall trial design will be a mixture of individually and cluster-randomized designs, with individual randomization done whenever possible. Clusters will consist of either contacts and contacts of contacts of index cases, that is, ring vaccination, or other transmission units.

**Results::**

The primary efficacy endpoint will be analysed as a time-to-event outcome. A vaccine will be considered successful if its estimated efficacy is greater than 50% and has sufficient precision to rule out that true efficacy is less than 30%. This will require approximately 150 total endpoints, that is, cases of confirmed Marburg virus disease, per vaccine/comparator combination. Interim analyses will be conducted after 50 and after 100 events. Statistical analysis of the trial will be blended across the different types of designs. Under the assumption of a 6-month attack rate of 1% of the participants in the placebo arm for both the individually and cluster-randomized populations, the most likely sample size is about 20,000 participants per arm.

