### Study sample size for individually randomized designs

The trial is endpoint-driven, as the primary analysis for each vaccine arm versus the concurrent shared placebo/control arm is triggered by occurrence of a total of 150 cases of MARV disease across these two arms. The primary analysis results will be reported but blinded follow-up will still continue. We assume a 1% cumulative attack rate in the control arm over 6 months of outbreak time. The trial period could involve several years of follow-up and across outbreaks. As stated above, there will be two interim analyses at the points when 1/3 and 2/3 of events have occurred, respectively. We use the O'Brien-Fleming-type spending function for both false-positive and false-negative errors. All the sample size calculations were conducted using the R package *rpact*.

For example, with a target level VE of 60%, with 150 total endpoints in a pairwise comparison, there is approximately 90% power to reject VE less than or equal to 30% if true VE is 60%, based on a logrank test with one-sided type I error rate of 0.025. With equal allocation to the active vaccine arm and the control arm, a minimum follow-up of 3 months for the last accrued participant and an annual drop rate of 10%, we calculated sample sizes for different accrual rates (Table 1). If on average 30,000 participants will be accrued each month, we need 18,062 participants per arm and an expected study duration of 9.1 months. Lower accrual rates are associated with longer study durations but smaller sample sizes. Using the sample size of 18,062 per arm, we simulated 100 times exponentially distributed event times without early stopping to investigate the coverage of the two-sided confidence interval of the VE estimate. The average total number of events is 179 and the average 95% confidence interval for the VE is (45%, 71%). The lower confidence bound would exclude 30% with a probability of 0.93, and the point VE estimate is greater than 50% with a probability of 0.91. We performed a sensitivity analysis, varying the accrual rate, assuming a 1% cumulative attack rate in the control arm over a 12-month period with an annual dropout rate of 10%, and a minimum follow-up of 6 months after the last accrual (Table 1). The sample size increases with increasing accrual rate to about 18,062 participants per arm. The best sample size is about 20,000 participants per arm, or about 40,000 participants per vaccine/comparator combination.

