### Study sample size for a mixture of individually and cluster-randomized designs

For those designs involving cluster randomization, the number of events needed to assess efficacy and sample sizes would be increased to account for the correlation within clusters. While the intraclass correlation coefficient (ICC) parameter for continuous and binary outcomes is commonly used, it is not easily extended to time-to-event outcome settings because of the presence of censoring (e.g. losses-to-follow-up, end-of-study administrative censoring).^
15
^ It has been shown that ICC estimators based on censoring indicators or observed event times can be negatively biased.^16,17^

One way to account for the clustering effect is using an ICC based on the binary event indicator and to inflate the events required by the usual design effect that equals 1 + (*m −* 1) ICC, where *m* is the average cluster size.^
18
^ For the Ebola ring vaccination trial in Guinea, the average ring size was about 80, and the ICC was about 0.05, resulting in a design effect of about 4. Thus, 600 total events would be needed for the design above, resulting in 150 effective events. For mixtures of individually and cluster-randomized designs, the target number of events will be the total number of effective events.

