^ is being deployed for the assessment of COVID-19 vaccines in multiple sites within multiple countries. This individually randomized, placebo-control trial fits roughly into category 1.a., in Figure 1. One important selection criterion for the Solidarity Vaccines trial populations has been to have an approximate 0.5%–1% COVID-19 cumulative incidence in the placebo arm over the average duration of follow-up. Other important selection criteria for sites include the ability to conduct the trial, including achieving targeted levels of enrolment and retention, and the need for more COVID-19 vaccines in the country. We propose building on the World Health Organization Solidarity trial design by adding the ability to assess the VE from transmission clusters and individual populations, to accelerate the case counts to meet the proposed endpoint totals. We allow for combining information across trial designs that involve both individual and cluster randomization. The goal would be to achieve an average 1% cumulative case incidence across the clusters. Because cluster-randomized designs require a substantially larger sample size than individually randomized trials, and because it is difficult to ensure comparability of baseline risk unless the number of clusters is very large, this design is less likely to be selected. The evaluation of performance characteristics for the blended analyses of individual and cluster-randomized would benefit from further investigation. Finally, like the World Health Organization Solidarity trial, we propose trial coordination of the different designs into a platform trial with a single steering committee and data monitoring committee. This proposed vaccine trial design can be implemented when MARV outbreaks occur, or for other emerging pathogens of high importance.

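### The abstract's figure of about 20,000 per arm for the blended trial comes from a calculation for individual randomisation only and should be labelled as such

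*Protocol article*

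**What the plan says.** The Abstract (Results) describes an analysis blended across designs and an event target: "This will require approximately 150 total endpoints, that is, cases of confirmed Marburg virus disease, per vaccine/comparator combination". It then gives the basis for the sample size, "Under the assumption of a 6-month attack rate of 1% of the participants in the placebo arm", and continues: "for both the individually and cluster-randomized populations, the most likely sample size is about 20,000 participants per arm".

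In the body, 20,000 per arm appears only under Study sample size for individually randomized designs. That section makes the same incidence assumption ("We assume a 1% cumulative attack rate in the control arm over 6 months of outbreak time"), obtains 18,062 per arm at an accrual of 30,000 a month, and rounds up to about 20,000.

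The next section, on mixtures of individually and cluster-randomised designs, inflates the required events by 1 + (m − 1) × ICC. It takes a ring size of about 80 and an ICC of about 0.05 from the Ebola ring trial, calls the design effect about 4, and concludes: "Thus, 600 total events would be needed for the design above, resulting in 150 effective events". For mixtures, the target is the total of effective events. No participant number is given for a cluster-randomised trial or for a mixture. The Conclusion says that "cluster-randomized designs require a substantially larger sample size than individually randomized trials" and that such designs are less likely to be chosen.

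**The concern.** The abstract attaches one participant number to a trial that contains both kinds of population, and the condition it states is equal incidence in the two. Equal incidence does not give equal information. At the same 1%, the article's own method discounts each event from a randomised cluster by the design effect. The number therefore carries over from individual randomisation to the blended trial without the adjustment that the body says is needed.

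Sponsors, sites and vaccine suppliers plan on participants and on outbreak time. If outbreaks lead mainly to ring randomisation, a plan built on 20,000 per arm and roughly 6 months of exposure would fall well short of the event target in that time, and nothing beside the figure warns of this.

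**Working it through.** **Inputs.**
- Test: "based on a logrank test with one-sided type I error rate of 0.025".
- Power: "there is approximately 90% power to reject VE less than or equal to 30% if true VE is 60"% (150 events).
- Control incidence: 1% over 6 months. Allocation 1:1, dropout 10% a year, minimum follow-up 3 months, accrual 30,000 a month (section on individually randomised designs).
- Ring size 80, ICC 0.05, design effect about 4 (section on mixtures).
- Assumption: exponential event and dropout times.

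**Step 1: reproduce the article's figure.** Monthly control hazard = −ln(0.99)/6 = 0.001675; vaccine hazard = 0.4 × 0.001675 = 0.000670; dropout hazard = −ln(0.90)/12 = 0.00878. With uniform accrual of 30,000 a month and analysis at 4.2 months (the last row of Table 1), 2 × 18,062 = 36,124 participants give about 149.6 events. With exactly 3 months after the last accrual, they give 149.8. Solving for 150 events gives 18,084 per arm against 18,062 stated. The figure is reproduced with no design effect, so it contains no allowance for clustering.

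**Step 2: events from 20,000 per arm, 6 months each.** The probability of an observed event is λ/(λ + δ) × (1 − exp(−6(λ + δ))), where λ is the event hazard and δ the dropout hazard. This gives 0.00974 (control) and 0.00391 (vaccine), a sum of 0.01365. Events = 20,000 × 0.01365 = 273.

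**Step 3: effective events if all are ring-randomised.** The formula gives 1 + 79 × 0.05 = 4.95; the article rounds to about 4.

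| Design effect | Effective events | Share of 150 | Actual events needed | Per arm at 6 months each |
|---|---|---|---|---|
| 4.95 | 273/4.95 = 55 | 37% | 150 × 4.95 = 742.5 | 742.5/0.01365 ≈ 54,000 |
| 4 | 273/4 = 68 | 45% | 150 × 4 = 600 | 600/0.01365 ≈ 44,000 |

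**Step 4: longer follow-up instead.** With the same hazards and accrual, 20,000 per arm reaches 600 events at about 14 months and 742.5 events at about 18 months of outbreak time.

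**Step 5: ring-randomised share that 20,000 per arm tolerates.** Let f be the share of participants randomised by ring, E the total events and D the design effect. Then E × [(1 − f) + f/D] = 150, so f = (1 − 150/E)/(1 − 1/D).
- 6 months each, E = 273: f = 0.4505/0.798 = 0.56 (D = 4.95), or 0.4505/0.75 = 0.60 (D = 4).
- At Table 1's 4.2-month final analysis, 40,000 participants give E = 163: f is about 0.10 for either D.

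**Step 6: dependence on cluster size.** With 273 events, the target is met as long as D ≤ 273/150 = 1.82. At ICC 0.05 this means m ≤ 1 + 0.82/0.05, about 17. For m = 5 there are about 227 effective events, and for m = 10 about 188. Neither falls short, even if everyone is cluster-randomised.

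**The case against.** The strongest reply is that the abstract never says 20,000 per arm is enough for an all-cluster trial. In its sentence, the reference to both populations qualifies the attack rate. The size is called the most likely one, and the article says individual randomisation will be used whenever possible. That is right, and for a mainly individually randomised mixture the figure holds (Step 5). What it does not answer is that the condition is unstated: the abstract gives no share, and its only stated premise is equal incidence.

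Second, the trial is event-driven, follow-up may run for several years and across outbreaks, and the target for mixtures is counted in effective events. This also stands. A reader might infer that a ring-randomised trial of this size would be analysed with about 54% to 63% power, or could never reach its trigger. The article does not support either inference. No analysis is triggered at 55 to 68 effective events, and the 6 months define the incidence rate without capping follow-up.

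Third, the ring size and ICC are borrowed as an illustration of one method. Clusters may also be households or compounds, and the article's wording about cluster designs in places includes design 1.b, where individuals are randomised within clusters and this inflation need not apply. This limits how far the figures reach, and Step 6 shows by how much. They remain the only values the article supplies, and its 600-event figure rests on them.

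**Conclusion.** The concern holds as a fault in the stated scope of the sample size. The figure of about 20,000 per arm is derived for individual randomisation alone, yet the abstract presents it for the blended trial, while the body says clustering raises the requirement.

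If all participants were randomised by ring, the information reached with 6 months each would be 37% (design effect 4.95) to 45% (design effect 4) of what is required. This rests on ring size 80, ICC 0.05, exponential times, true VE of 60% and 10% annual dropout. The cost would fall on participants or time, with power preserved by the effective-event target. It would also be wrong to read this as applying to cluster randomisation in general, since small clusters at the same ICC show no shortfall.

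**What to change.** In the Abstract and in the section on individually randomised designs, state that about 20,000 per arm applies to individual randomisation or to a mainly individually randomised mixture.

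Add a line, labelled as illustrative under ring size 80 and ICC 0.05:
- With 6 months of follow-up each, 20,000 per arm yields 150 effective events only if at most about 56% to 60% of participants are ring-randomised (about 10% at Table 1's 4.2-month analysis).
- A mostly ring-randomised trial needs more participants or longer follow-up.

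The 44,000 to 54,000 per arm should not be entered as a design constant, because it depends on illustrative values and on exactly 6 months each. The cost is a rewording and one line of figures. The event target and the analysis need no change, though the stated size will look less favourable for ring settings.

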**Conclusion::**

This event-driven design takes into the account the potentially sporadic spread of Marburg virus. The proposed trial design may be applicable for other pathogens against which effective vaccines are not yet available.

## Background

The World Health Organization was notified on August 3, 2021 of a confirmed case of Marburg virus (MARV) disease in the Guéckédou prefecture in the Republic of Guinea.^
1
^ As this was the first time MARV disease was detected in the country, concerns were raised about a possible epidemic. Fortunately, no additional MARV disease cases were detected in the area.^
2
^ Nevertheless, the emergence of MARV in Guinea highlights the continued presence of filoviral diseases in Central and Western Africa, and strongly suggests that, before the rapid implementation of diagnostics and surveillance that followed the Ebola virus epidemic in West Africa in 2014,^
3
^ many outbreaks may have gone undetected. Predictably, since 2014, cases of filovirus disease have been seen annually. Moreover, filovirus sequences (including MARV and Bombali virus) have been identified in bats in West Africa,^4,5^ suggesting that MARV and other filoviruses are endemic in rainforest areas of Sub-Saharan Africa. Importantly, in contrast to Ebola virus, currently there are no licenced vaccines against MARV. To enhance the rapid development of MARV vaccines, the World Health Organization R&D Blueprint has convened a group of experts from industry, government and academia to share knowledge, assays, laboratory networks and animal models with the ultimate goal to promote preclinical and clinical development of MARV vaccine candidates.^
6
^ This World Health Organization-coordinated consortium for the development and evaluation of MARV vaccines is based on the same sharing principles that governed the scientific interactions of the World Health Organization COVID-19 working groups and that accelerated the development of COVID-19 vaccines^
7
^ and therapeutics.^
8
^ A number of Marburg virus vaccine candidates are in the pipeline. A DNA–MARV vaccine was manufactured and showed favourable safety and immunogenicity in trials in both the United States and Africa, but is not actively being advanced into clinical development.^
6
^ Currently, five vaccines are in, or planned for, clinical development – two adenovirus (Ad)-based vector vaccines and three vesicular stomatitis virus (VSV)-based vector vaccines.^
6
^

In this report, we summarize current insights from ongoing efforts by a World Health Organization R&D Blueprint working group on the design of randomized Phase 2b and 3 vaccine efficacy (VE) trials for candidate MARV vaccines that should soon be ready for testing. These trial designs will accommodate the complex epidemiology of MARV transmission by allowing for accumulation of evidence over multiple outbreaks that occur at different times and locations. It should be recognized, however, that such designs would not be feasible to implement unless the outbreaks that emerge are much larger than most of those documented so far. As we saw with Ebola (and of course COVID-19), it is almost impossible to know if or when such outbreaks might occur. However, it is extremely important to implement vaccine trials rapidly when infectious disease threats unexpectedly occur.^
9
^

## Methods

### Operating characteristics of the trial design

A core protocol approach will be used, allowing multiple vaccine candidates to be tested against a shared placebo/control group. The primary objective of the trial will be to evaluate the effect of each vaccine on the rate of virologically confirmed MARV disease, regardless of severity. In some cases, it may also be possible to evaluated MARV infection as a co-primary outcome. Although the study may lack power for formal statistical inference about VE against severe disease or death due to MARV disease, these secondary endpoints will be evaluated and reported for each vaccine. Additional exploratory endpoints will include VE between the first and second dose, for two-dose vaccines. Infecting viruses will be sequenced as much as possible to assess the influence of virus clades and evolution on transmissibility, virulence and VE. A subset of trial participants will provide periodic blood samples. Immune markers measured from participants in this immunogenicity subset will be used to assess immune correlates of risk and protection, and help with the assessment of VE against infection.

The trial is endpoint-driven, as the main analysis for each vaccine arm versus the concurrent shared placebo/control arm is triggered by the occurrence of a total of 150 cases of MARV disease across these two arms. While results from the main analysis will be reported, blinded follow-up will continue to evaluate safety and duration of immunity. This fixed number of 150 endpoints provides 90% power to rule out the hypothesis that VE is ≤ 30%, when the true VE is ≥ 60%, where statistical significance would be achieved if the estimated VE were ≥ 50%. In the setting of COVID-19 vaccines, such results would meet or exceed the World Health Organization-Food and Drug Administration (FDA) established threshold for worthwhile VE.

A global data monitoring committee will regularly review the accumulating safety results and major endpoint results. Different candidate vaccines may be available or suitable to enter the trial at different calendar times. Using a shared placebo/control group and a common core protocol to evaluate multiple candidate vaccines in the trial, resources allocated to the evaluation of each candidate vaccine will be judiciously saved while a high standard of scientific rigour and efficiency is ensured.^
10
^ Participants will be randomized to one of the vaccines (k in number) for which they are eligible or to one of the placebos that correspond (in appearance, dosing interval, and route of administration) to each of those vaccines. The randomization ratio will ensure that participants have the same chance of receiving a placebo (with probability 1/(k + 1) for placebo in aggregate, which is the sum of the probabilities 1/k(k + 1) for each individual placebo) as they have of receiving each individual vaccine (with probability 1/(k + 1)) for which they are eligible. Outcomes in recipients of each vaccine candidate will be compared with outcomes in all placebo recipients who were eligible to be randomized to that vaccine. This approach preserves blinding and enables comparison of each vaccine’s results directly to results from an equal number of controls who received placebo at the same time and place. Groups of sites in specific countries or subsets of sites across countries may want to collaborate in making further measurements or observations. These could be thought of as Phase 2b trials nested within the Phase 3 trial, provided that they also collect all information needed for the Phase 3 trial. Well-organized additional research studies could be conducted to assess additional secondary and supportive endpoints, such as infection or viral load (as a surrogate for transmission); nonetheless, they are not core requirements for all sites. For cluster-randomized designs, both indirect and overall vaccine effectiveness can be estimated as additional exploratory endpoints.

The trials will be double-blind to the extent possible. The best comparators will be either vaccine placebos or active comparator vaccines that are not related to protection from MARV infection, but would provide benefit to the population, for example, hepatitis A vaccine; however, a vaccine comparator could complicate safety assessments. If neither is possible, then observation-only or delayed vaccination may be used for this purpose.

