## Results

### VE analysis

The primary efficacy endpoint will be analysed as a time-to-event outcome, including only those events that occur 10 days after the final vaccination dose. Such a gap of 10 days is chosen to allow time for the vaccination series to take effect and to reduce the chance of including events occurred prior to the vaccination due of the incubation period for Marburg. All participant-level failure (diagnosis with disease) and censoring events are reported relative to the time of randomization. The time of virologically confirmed (i.e. laboratory-confirmed) MARV disease is the earliest time of reported qualifying MARV disease symptoms that occur within 10 days of virological confirmation of MARV infection. Participants’ follow-up times will be right censored at the time of last contact at which endpoint status was assessed. Cox proportional hazards regression will be used for analysis. VE, measured by one minus the hazard ratio (vaccine versus placebo/comparator), will be the effect measure. Inference will be based on a one-sided logrank test of H_0_
^benefit^: VE ≤ 0.30, using an O'Brien-Fleming boundary for early termination that preserves an experimental (one-sided) 0.025 error rate; the alpha levels would be one-sided 0.0003 at 50 events and one-sided 0.0069 at 100 endpoints, where the remainder of the (one-sided) 0.025 error rate would be spent at the final analysis. Using these O'Brien-Fleming criteria after 50 and 100 events, benefit is established when estimated VE is ≥80% and ≥59%, and lack of benefit, that is, ruling out the target VE of 60% for which the trial has 90% power, is established when estimated VE is ≤−6% and ≤34%, respectively. When estimating VE against infection, the outcome would be infection as measured by time to seroconversion, using interval censoring methods for the estimand. In this case, the operating characteristics of the statistics would be the same as described above.

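### When vaccines with different times to final dose share a placebo pool, the stated counting rule starts controls in one comparison on different days and biases VE

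*Protocol article*

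**What the plan says.** Four statements in the article have to be read together.

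- **Placebos (Operating characteristics of the trial design).** Participants receive one of the k vaccines or one of the "placebos that correspond (in appearance, dosing interval, and route of administration) to each of those vaccines". Each individual placebo has probability 1/k(k + 1), so the placebo group is split equally over the k schedules.
- **Comparator (same section).** Each vaccine's outcomes are "compared with outcomes in all placebo recipients who were eligible to be randomized to that vaccine", which pools all the placebo types.
- **Schedules (same section).** An exploratory endpoint is "VE between the first and second dose, for two-dose vaccines", so vaccines with more than one dose are foreseen. No dose interval is stated anywhere.
- **Counting and clock (VE analysis).** The primary endpoint is a time-to-event outcome "including only those events that occur 10 days after the final vaccination dose". Failure and "censoring events are reported relative to the time of randomization". Follow-up is right censored at last contact. Neither delayed entry into the risk set nor a single counting window per comparison is mentioned.

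The main analysis is "triggered by the occurrence of a total of 150 cases of MARV disease across these two arms", with interim looks at 50 and 100 events.

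**The concern.** Take one one-dose and one two-dose vaccine running together. A two-dose vaccinee who falls ill between day 10 and the tenth day after dose 2 contributes no event. In the same comparison, a control who received the one-dose placebo and falls ill on the same day does contribute one. If everyone is in the risk set from randomization, the control arm collects extra events that the vaccine arm cannot, and VE is inflated. For the one-dose vaccine the mismatch runs the other way: half of its controls are barred from early events that its own recipients can contribute.

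The comparison is then no longer like for like, although randomization made it so. The primary estimate, the type I error against the 30% hurdle and the power are all affected, and the platform favours longer schedules over shorter ones. The article fixes the comparator set, the event window and the time origin itself, so this is a problem in the stated rules and not just a detail left for later.

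**Working it through.** **1. The plan's own figure.** The article says 150 events "provides 90% power to rule out the hypothesis that VE is ≤ 30%, when the true VE is ≥ 60" percent, "based on a logrank test with one-sided type I error rate of 0.025". With HR 0.70 under the null and 0.40 under the target:

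- ln(0.70/0.40) = 0.5596
- null SE = √[(1.7²/0.7)/150] = 0.166; alternative SE = √[(1.4²/0.4)/150] = 0.181
- power = Φ[(0.5596 − 1.96 × 0.166)/0.181] = 90.3%

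The stated 90% is reproduced when both arms are counted alike.

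**2. Rejection rule used below.** Of 150 events, the vaccine arm's share is p = HR/(1 + HR). Under the null p = 0.7/1.7 = 0.412, giving mean 61.8 and SD 6.03. With a final boundary of z = 2.003, success needs at most 49 vaccine events. With aligned windows the exact binomial gives 2.0% false success at true VE 30% and 88.4% power at true VE 60%. Only the final look is evaluated.

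**3. Bias formula.** Let w₁ and w₂ be the mean counted days per person on the one-dose and two-dose schedules. For rare events, constant hazard, k = 2 and everyone at risk from randomization,

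observed HR ≈ true HR × w(own) / [(w₁ + w₂)/2].

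**4. Inputs.** From the article: 36,124 participants at 30,000 a month (accrual lasts 1.204 months), 1% control attack rate over 6 months (hazard −ln 0.99/6 = 0.001675 a month) and 10% annual dropout. Assumed: k = 2 and dose intervals of 14, 28 or 56 days. Because the trial is event-driven, the windows are taken at the time when 150 *counted* events are expected.

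Worked case (28 days, two-dose vaccine, true VE 30%): the 150th counted event falls at about 4.57 months. Mean follow-up is (4.57 − 0.602) × 30.44 = 121 days, so w₁ = 121 − 10 = 111 and w₂ = 121 − 38 = 83. Observed HR = 0.70 × 83/97 = 0.599, so VE reads 40%. Then p = 0.599/1.599 = 0.375, and P(at most 49 of 150) is about 13%.

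| 30,000/month | 14 days | 28 days | 56 days | aligned |
|---|---|---|---|---|
| Two-dose, true VE 30%: w₁/w₂ | 101/87 | 111/83 | 131/75 | |
| VE reads | 35% | 40% | 49% | 30% |
| False success | about 6% | about 13% | about 44% | 2% |
| One-dose, true VE 60%: w₁/w₂ | 115/101 | 121/93 | 131/75 | |
| VE reads | 57% | 55% | 49% | 60% |
| Power | about 80% | about 69% | about 42% | 88% |

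Hand calculation from the rounded windows lands within about two points of these probabilities.

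**5. Slower accrual.** In the 1,000/month row the windows are 257/243, 268/240 and 290/234 days. The two-dose vaccine with true VE 30% reads about 32%, 34% and 38%, with false success about 3%, just over 4% and about 9%.

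**6. Separate check.** With a fixed 6 months of follow-up and a 28-day interval, w₁ = 172 and w₂ = 144, so VE reads 1 − 0.70 × 144/158 = 36%; with 56 days it reads 44%. Simulated Cox fits (20,000 per arm, 400 replicates) without delayed entry gave 36.8% and 44.0%. With delayed entry, or with one common window, they gave 30.7% and 29.9%. If the hazard is front-loaded (assumed exponential decay with mean 42 days), the 28-day case reads 53%.

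**7. Triggers under delayed entry.** In the two-dose comparison, one-dose placebo events between day 10 and the opening of the two-dose window have no vaccinee at risk and carry no information. At 30,000/month, 28 days and true VE 60%, w₁ = 129 and w₂ = 101. The uninformative share is (28/2)/(0.4 × 101 + 115) = 14/155.4 = 9%, or about 14 of the 150 triggering events.

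**The case against.** The strongest reply is that the text does not prescribe mismatched windows. It refers to the final dose without saying whose schedule governs a control borrowed from another vaccine's placebo. Reporting times from randomization sets a time scale and does not rule out delayed entry on it, which would remove the bias. The article also says the estimand will be fully pre-specified, speaks well of the treatment-policy estimand, and calls the post-vaccination window a variation to be considered. Counting all events from randomization leaves no mismatch.

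Much of this stands as a limit on certainty. It does not dispose of the point. The VE analysis section states the 10-day rule flatly as the primary analysis and describes right censoring only. The natural reading of a post-dose window is the participant's own dose. Delayed entry, if intended, still leaves the triggers undefined (step 7).

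The common vaccination schedule mentioned with Figure 1 sits under design 1.a only and concerns a vaccine and its comparator. Extended to the platform, it would conflict with placebo-specific dosing intervals.

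Two stronger readings are tempting, and the documents do not support either.

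- **That VE is biased in every comparison.** It is not with k = 1, with equal times to final dose, or where eligible participants share one schedule. The article does not say that one-dose and two-dose vaccines will run concurrently with overlapping eligibility.
- **That the bias can be read off at Table 1's 4.2-month final look.** With a 56-day interval this would give VE 57% and 80% false success for the two-dose vaccine with true VE 30%. But only about 99 counted events exist by then; the 150th arrives near 5.2 months, where the figures are 49% and 44%. The 30,000/month row is also the fastest accrual in the table.

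**Conclusion.** The concern holds conditionally. When vaccines with different times to final dose share a placebo pool, the rules as written make controls within one comparison start counting on different days, inflating VE for the longer schedule and deflating it for the shorter.

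The direction follows from the text. The size does not, because no interval is given. Across the assumed 14 to 56 days it runs from about 2 to 8 VE points for the two-dose vaccine at 1,000/month to about 5 to 19 points at 30,000/month. Type I error ranges from barely above the aligned 2% to many times that. The figures rest on k = 2, constant hazard, everyone at risk from randomization and analysis at the 150th counted event. Longer follow-up shrinks them (12 months with a 28-day interval reads 61.6% for a true 60%), and a front-loaded hazard enlarges them. This should be settled before vaccines with unequal schedules share controls.

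**What to change.** Add one sentence to the VE analysis section: within each vaccine-control comparison, both arms, including every pooled placebo recipient whatever placebo schedule they followed, start event counting and risk time on one common day since randomization, namely the tested vaccine's scheduled final-dose day plus 10. Use the same count for the 50-, 100- and 150-event triggers.

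An acceptable alternative is delayed entry, with each participant entering the risk set when their own window opens, provided that events occurring before both arms are at risk do not count toward the triggers.

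The statement about a common vaccination schedule (Figure 1, design 1.a) and the placebo-specific dosing intervals (Operating characteristics) must also be reconciled.

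The cost is text only: no added participants, visits or data, no change to dosing, and the shared control group is kept in full. Because early events are excluded, the 150th counted event comes somewhat later than Table 1 shows, but the 10-day rule already implies such a delay.
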